## Abstract

**Background:**

Distinct molecular, inflammatory, and metabolic signatures are present in oocytes and follicular fluid derived from women with obesity when compared to those derived from normal weight women, which suggest existing signals that may program future offspring for metabolic diseases. This study aims to assess the feasibility and efficacy of a peri-conception nutrition and exercise intervention on mitigating obesity-associated changes in oocyte gene expression profiles and follicular fluid metabolites.

**Methods:**

This single blinded randomized control trial will include 120 women with a BMI of 25–45 kg/m^2^, ≥21 years of age, and undergoing in vitro fertilization (IVF) treatments. Participants will be randomized to standard of care (*N* = 60) or an intervention group (*N* = 60) in a block design by polycystic ovary syndrome status. The intervention will combine a dietary component (Mediterranean meal plan) with exercise prescription following the Physical Activity Guidelines for Americans. Participants will be assessed pre- and post-intervention. The standard of care group will be offered to join the intervention group if the IVF treatments are unsuccessful as a cross over design. Recruitment is anticipated to start in July of 2021. Primary outcomes will include single oocyte gene expression profiles and follicular fluid metabolites. Mann-Whitney U nonparametric tests will be used to assess potential differences for each stratum. Follicular fluid and serum metabolites will be analyzed using a one-factor Analysis of Covariance (ANCOVA) at four levels, pair-wise comparisons using Tukey-Kramer post-hoc tests will be used to identify groups whose means differ significantly while retaining the family-wise error rate at 5%. When the design is balanced, two-way Analysis of Variance (ANOVA), or non-parametric Friedman test will be used in data analysis. Additionally, general linear models and ANCOVA may be used to control for covariates. Significance will be set at *p* < 0.05. Findings will be disseminated via peer-reviewed manuscripts and presentations at scientific conferences.

**Discussion:**

This study will provide novel data and key information on the impact of a dietary and exercise intervention on oocyte gene expression and follicular fluid content. Results will demonstrate the potential of such intervention in mitigating obesity-induced changes in oocyte gene expression and follicular fluid metabolites.

**Trial registration:**

ClinicalTrials.gov (NCT04273048): submitted November 13, 2019; posted February 17, 2020.

## Background

Because of obesity’s increasing prevalence and limited treatment success, one approach to stem the obesity epidemic involves reducing the risk of obesity as early in life as possible. The Developmental Origins of Health and Disease (DOHaD) hypothesis suggests there are critical windows of development and growth, such as the in utero environment, that may significantly impact health for years to come through metabolic programing [1]. Undernutrition during this time alters metabolic tissues and systems in ways that confers vulnerability to cardio-metabolic diseases such as metabolic syndrome [2]. Research demonstrates that peripheral organ development is adversely affected by maternal obesity, with sex-specific changes in metabolic, cardiovascular, immune, and microbiome physiology in offspring, which may be transmitted through placental adaptations for lipid accumulation, altered nutrient transport, inflammation, and oxidative stress [3]. Similarly, other research involving experimental animals focused on manipulating the maternal diet during pregnancy and impairing fetal nutrition showed permanent changes in tissue structure, body composition, endocrine responses and metabolism in the offspring and a vulnerability to adult hypertension and diabetes [4]. Epidemiological analyses demonstrated that lower birth weight is a risk indicator for adult cardiovascular disease, hypertension, type 2 diabetes and metabolic syndrome (cardio-metabolic disease) [1]. Maternal obesity during pregnancy confers a major risk to offspring obesity [5], but less is known about the impact of peri-conception factors that influence metabolic programming. This research evolved into the concept of metabolic programming, where early periods of development have critical impact on multiple organ systems and lead to vulnerability to cardio-metabolic disease [2].

We have reported distinct molecular, inflammatory, and metabolic signatures in single oocytes and follicular fluid derived from obese women when compared to normal weight women preparing to undergo in vitro fertilization (IVF) [6]. The molecular disturbances found in oocytes of overweight women could be mitigated through an intervention involving a healthier diet and increased physical activity (PA) during the peri-conception period [7–9].

Models of diet-induced obesity in mice have shown that exercise improves, but does not reverse, damage imparted on oocytes as a result of a high fat diet [10]. A systematic review and meta-analysis of human studies found that exercise improved pregnancy rates (risk ratio 2.10, 95% CI: 1.32–3.35) in women with reproductive health problems like polycystic ovary syndrome (PCOS) [11]. Studies have also demonstrated promising maternal-fetal benefits of exercise during pregnancy such as improved physical fitness [12], more appropriate gestational weight gain [13], a decreased risk for preeclampsia and other pregnancy-specific diseases like gestational diabetes [14, 15], and decreased odds of macrosomia at birth without affecting the odds of growth-restricted, preterm, or low birth weight babies [12, 16, 17]. Studies have demonstrated that adherence to a Mediterranean diet, characterized by higher intake of unsaturated fats, lower intake of animal fats, and lower ratios of omega-6 to omega-3 fatty acids [18], is also associated with a reduced risk of many chronic diseases [19], improved fertility rates [odds ratio 1.4, 95% CI: 1.0–1.9] [20], as well as larger embryo yield in IVF [21], and better pregnancy outcomes [7, 20, 22, 23].

Despite the evidence of a healthier diet improving IVF procedure outcomes, there is little evidence on the molecular changes at the level of the oocyte or follicular fluid that occur due to alterations in diet, and virtually nothing is known about the impact of the combined effect of healthy diet and increased PA. Thus, we have designed a study with the primary objective of assessing the efficacy of a peri-conception nutrition and exercise intervention on mitigating obesity-associated changes in oocyte gene expression profiles and follicular fluid metabolites. Secondary objectives include determining the effect of the intervention on cumulus cells gene expression as well as the feasibility and acceptability of the intervention (using a standardized taxonomy [24]). To help address these objectives, overall metabolic health indices such as fitness, blood pressure, insulin sensitivity, triglycerides, C-reactive protein and interleukin-6 concentrations will be assessed.

## Methods

This is a single-blinded randomized control trial testing the efficacy of a dietary and exercise intervention for women with overweight and obesity undergoing infertility treatment. Ethical approval was obtained from the UAMS Institutional Review Board (UAMS IRB-260113), version 10 of the protocol. This article follows the SPIRIT (Standard Protocol Items: Recommendations for International Trials) guidelines for reporting clinical trial protocols [25]. Table 1 and Fig. 1 detail the time schedule of enrollment, interventions, and assessments. Findings will be disseminated via peer-reviewed manuscripts and presentations at scientific conferences, at which time protocol amendments will be discussed.

**Table 1 Tab1:** Schedule of enrollment, interventions, and assessments at specific time points

			Study Period			
	Staff Member	Pre-study Screening/ Consent	Baseline	Allocation		Post-Allocation
**Time Point**			Visit 1	Visit 2	Visit 3	Retrieval
RECRUITMENT/ENROLLMENT						
Eligibility Screen	Research Team Member	x				
Medical Record Release and Medical Release for Exercise	Medical Provider/Arkansas Fertility and Gynecology	x				
Informed Consent	Research Team Member		x			
Allocation of Treatment Groups	Clinical Coordinator or PI			x		
Compensation	Research Team Member		x		x	x
INTERVENTION						
Diet, Exercise, Coaching*	Research Team Member		x	x^1^	x^1^	x
Standard of Care	Arkansas Fertility and Gynecology		x	x	x	x
ASSESSMENTS						
Demographic and Contact Information	Research Team Member		x		x	
Medical History	Research Team Member		x		x	
Vitals and Anthropometrics	Research Team Member		x		x	
Fasted blood collection	Phlebotomist		x		x	
Urine sample collection	Participant		x		x	
Stool sample collection	Participant		x		x	
Body Composition	Research Team Member		x		x	
Resting Energy Expenditure	Research Team Member		x		x	
Activity Energy Expenditure	Participant Worn Monitor		x		x	
Fitness Testing	Exercise Physiologist		x		x	
3 Day Food Records	Nutritionist		x			
Coaching	Research Team Member			x^1^	x^1^	
Physical Activity Questionnaire	Participant Self-Assessment		x		x	
Cohen’s Perceived Stress Scale	Participant Self-Assessment		x		x	
Beck Depression Inventory-II	Participant Self-Assessment		x		x	
Oocyte and Follicular Fluid Retrieval	Arkansas Fertility and Gynecology					x
Hormonal Panel and Birth Outcomes	Arkansas Fertility and Gynecology					x
Feasibility Qualitative Interviews	Research Team Member					x^1^

x- All Participants, x^1^-Only the intervention group, * Diet, Exercise, and Coaching will take place after Visit 2 of study, intervention will last 8–12 weeks depending on oocyte retrieval process

**Fig. 1 Fig1:**
[figure not shown]
Study Flow Chart. Protocol schematic diagram including informed consent, visits, randomization, intervention and control groups, fertility clinic procedures, and cross over design. AF&GA: Arkansas Fertility and Gynecology Associates, BMI: Body Mass Index

### Study setting

This multi-component intervention will be conducted primarily via telemedicine, thus the location will vary and may include places like the participants’ homes or a local gym. Participants will be undergoing fertility treatments at Arkansas Fertility and Gynecology Associates (AF&GA), which serves Arkansas and surrounding states. Data collection will take place within AF&GA and the Arkansas Children’s Nutrition Center (ACNC), both of which are located in Little Rock, Arkansas.

### Eligibility and recruitment

Criteria for study inclusion are women with a BMI between 25 and 45 kg/m^2^, age of 21 years or over, and planning to undergo in vitro fertility treatment. Participants reporting the following will be excluded from the study: pre-existing conditions (e.g. sexual transmitted diseases) that will affect the outcomes of the study as determined by the principal investigator; current use of recreational drugs, tobacco, nicotine, or alcohol; food allergies, food intolerances, or food preferences which would interfere with compliance to the meal plan; and contraindications to exercise or already meeting the Physical Activity Guidelines for Americans [8] (150 min moderate activity/week or 75 min of vigorous activity/week with resistance exercise on 2 or more days/week.

Recruitment of participants will be conducted by the AF&GA team using IRB-approved tools. Advertisements and information sheets will be distributed to eligible participants electing to undergo fertility treatments. Women who are interested in participating in the study can inform the AF&GA team, call the ACNC recruitment line, send an e-mail expressing their interest, or express their interest through the ACNC website. To establish eligibility for participation in the study, a standardized questionnaire will be administered by phone.

### Consent and randomization

The informed consent process will educate potential participants about the research study through IRB-approved methods. Eligible participants will be contacted, and a copy of the informed consent will be provided to the participant prior to signing consent documents. A research team member will reach out to potential participants 2 days prior to the scheduled visit to perform a COVID-19 screening and answer questions on the intervention components of the study. At the first visit, the research team will review all study procedures and the informed consent documents with the potential participant. Participants will be given sufficient time to review the consent form, ask questions, and receive clarification prior to signing any documents. If eligible and interested in enrollment, informed consent will be obtained from the participants and documented.

Women will be randomized, with computer generated randomization, to a standard of care group (*N* = 60) and an intervention group (*N* = 60). Due to the high incidence of obese women with Polycystic Ovarian Syndrome (15–30%) [26], compared with other infertility diagnoses, women will first be classified into one of two strata based on the presence or absence of PCOS. Within each stratum, the proposed study will randomize the enrolled participants into either the intervention group (*N* = 30) or the standard of care group (*N* = 30). Thus, the potential for confounders of infertility, besides PCOS, should be equally distributed between the groups and not affecting the main outcome of interests. The study will have four experimental arms: PCOS-standard of care, PCOS-intervention, no PCOS-standard of care, no PCOS-intervention. Allocation will happen at the second visit (after consent and the collection of baseline measures) by providing the participant with an opaque, sealed envelope containing their allocation.

### Interventions

The intervention, combining an exercise and a dietary component along with the standard practice from AF&GA, will take place during the weeks leading up to oocyte retrieval and continue until 2 weeks after implantation. We expect the intervention to last 8–12 weeks, depending on the participant’s specific fertility treatment plan.

The intervention will be delivered by trained research team members who will meet with participants twice weekly and serve as their health coach in order to track compliance and support adherence to the meal and exercise plan. This contact will occur via their preferred contact method (e.g., telephone, text messages, email, or using applications such as FaceTime). All interventionists will complete an intensive training on the intervention protocol and motivational interviewing techniques [9, 27]. They will be provided with detailed counselor guides to follow. Prior to conducting a coaching session with a participant, they will be required to be certified by one of the study investigators in providing both initial and subsequent intervention sessions. All sessions will be video or audio recorded; 15% of sessions will be randomly selected, reviewed, and scored on a fidelity rating scale to ensure that the protocol is being implemented as intended. Fidelity ratings will include building and maintaining rapport; discussion of daily meal plan adherence and compliance; discussion of weekly exercise adherence and compliance [28]; use of SMART goal setting techniques [29]; engagement with participant in problem solving as needed; and use of reflective listening, positive reinforcement, and summarizing techniques [30]. Feedback will be provided to the coach on every session reviewed.

#### Exercise intervention

The exercise intervention will be based on the Physical Activity Guidelines for Americans for exercise prescription (150 min of moderate exercise per week and muscle strengthening exercises on two or more days per week). The exercise program will be customized to the participant and delivered using a web- and mobile-based application. The exercise program will be built for 8 to 12 weeks, depending on study length, with increasing intensity of combined aerobic and resistance exercises over the course of the study. The goal is for participants to perform at least 3 routines per week at their desired location. Total session time may vary by participants depending on number of breaks and rest periods. Exercise routines will combine aerobic, resistance and stretching exercises. In addition, participants will be encouraged to walk daily and increase their daily steps by 500 steps per day every week until they reach 10,000 steps per day. They will be able to monitor their steps with provided pedometers (Fitbit, Garmin, Apple Watch, etc.). Participant’s adherence to their exercise prescription and walking goal will be assessed weekly by the coach.

#### Dietary intervention

The dietary intervention is based on the Mediterranean diet. The meal plan was designed by a Registered Dietitian and follows the 2015 Dietary Guidelines for Americans healthy Mediterranean-style eating pattern (Tables 2 and 3) [31]. Participants will be provided with all meals (3 meals/day) throughout the 8–12-week intervention that are in compliance with the Mediterranean diet in the form of refrigerated packaged meals from a company with the capacity to provide made-to-order meals and deliver them to the participant’s home address. The meals will be heated using conventional equipment found in most households and require no further preparation. Depending on calorie and macronutrient requirements, as assessed by the coach in accordance with participant feedback, snacks that adhere to the Mediterranean meal plan may be added. Snacks will include nutrient dense foods such as whole grains, fruits, nuts, low-fat milk, yogurt, and/or cheese. This nutrition intervention is not designed for participants to lose weight, however with the meal plan that could occur. Participants will be provided with a detailed weekly meal plan and will be asked to keep record of what they eat daily, on paper and/or using RedCap surveys.

**Table 2 Tab2:** Dietary Guidelines for Americans Mediterranean-Style Meal Pattern

Food Group	Daily Goal^a^
Vegetables	2.5 c-eq.
Fruits	2 c-eq.
Grains	6 oz.-eq.
Dairy	2 c-eq.
Protein	6 oz.-eq.
Oils	24 g

^a^Expressed as cup-equivalents or ounce-equivalence in accordance with the Dietary Guidelines for Americans standard practice [32]

**Table 3 Tab3:** Example menu day

Meal	Food Group Pattern^a^	Example Menu Items
Breakfast	1 c-eq fruit	1 Medium Apple
	2.8 oz.-eq grains	1 Blueberry Bagel
	1 c-eq dairy	2 Low-fat Cream Cheese Wedges
	1 oz.-eq nuts	1 Snack Pack Mixed Nuts
Lunch	2.5 c-eq vegetables, 1.3 oz.-eq grains, and 5.5 g oils^b^	Pesto Pasta with Sautéed Greens, Carrots, Tomato, and Zucchini Mixed Dish
Dinner	4 oz.-eq protein	Salmon
	2.5 c-eq vegetables, 1.3 oz.-eq grains, and 5.5 g oils^b^	Smoked Paprika Vegetables (sautéed broccoli, carrots, kale, and tomato), and Brown Rice Mixed Dish
	13.5 g oils	1 TB Olive Oil
Snack	1 c-eq fruit	2 Clementines
	0.6 oz.-eq grains	5 Multi-Grain Crackers
	1.1 c-eq dairy	2 Light String Cheese Sticks
	1 oz.-eq protein	3 Slices Deli Turkey Breast

^a^Equivalents are obtained through NDSR and rounded to the nearest tenth

^b^Mixed dish equivalents are based on 7 randomly selected vegetarian line meals from the food vendor

#### Standard of care

Participants in the standard of care group will be provided with dietary and physical activity recommendations from the Dietary Guidelines for Americans at their first study visit and will follow the standard of care practice at AF&GA up to their retrieval procedures. Participants will not be required to wait 8 weeks prior to their retrieval procedures since no intervention is needed. If participants in the standard of care group plan to undergo a second oocyte retrieval cycle, they will be offered to join the intervention group at that time as a cross over design.

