##### Oocyte, cumulus cell, and follicular fluid data collection

AF&GA will provide the research team with oocytes (eggs), cumulus cells (cells surrounding the egg), and follicular fluid (liquid surrounding the egg that also contains granulosa cells) that are not needed for the IVF procedures (e.g., too many eggs retrieved). These samples will be collected during the standard oocyte retrieval procedures performed as part of standard care for the participants undergoing fertility treatment. Participants will undergo standard procedures at AF&GA for ovarian stimulation, which include hormonal superovulation and oocyte retrieval 36 h after human gonadotropin injection. Any deviations from the standard clinic procedures will be documented and sensitivity analyses will be performed to determine whether deviations to stimulation protocol yielded in significant differences. It is possible that the research team will not obtain samples in the case that the retrieval yields only enough eggs for the IVF procedures. In this case, only follicular fluid will be obtained. The research team will not obtain samples that could have been fertilized or frozen as agreed with the participant prior to the retrieval procedure. The research team will obtain only samples that are unneeded by the clinic. Thus, no additional treatment or clinical procedures will be required for the participants. The embryologist at the clinic will collect the cumulus cells during the processing of the oocytes. Granulosa cells will be isolated from the follicular fluid by centrifugation at 4000 rpm for 10 min. Follicular fluid samples contaminated with blood will not be used for analysis. Samples will be placed on ice and transported by the research team to the ACNC where they will be stored in messenger RNA lysis buffer and frozen at − 70 °C until processing. Oocytes and cumulus cells will be used to study gene expression while follicular fluid will be used to measure metabolites and hormones that may be influenced by diet and exercise. Both mRNA and genomic DNA will be isolated from individual oocytes as previously described [9]. cDNA libraries will be prepared and fragmented cDNA will be evaluated to determine size distribution of the libraries. Samples will be sequenced using the NextSeq 500 System (Illumina). Individual libraries will be generated and RNA-Seq will be conducted. Sequencing reads from each sample will be trimmed and filtered before being aligned to the human genome (hg19). All data will be analyzed using SeqMonk and R software. Differentially expressed gene expression will be identified using the DESeq2 package which will include multiple testing corrections. Serum and follicular fluid glucose, total cholesterol, and triglyceride levels will be assessed using colorimetric or electrochemiluminescence assays. Serum and follicular fluid insulin, leptin, tumor necrosis factor (TNF)-α, C-reactive protein (CRP), and interleukin-6 will be measured using enzyme-linked immunosorbent or electrochemiluminescence assay kits. Serum lipid profiles—non-esterified fatty acids, high-density lipoprotein, and low-density lipoprotein— will be analyzed by enzymatic methods on a clinical analyzer. All assays will be performed in accordance with the manufacturers’ instructions.

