#### Sample size

Based upon existing data in the literature, a power of 0.8, and a *p*-value set at 0.05, with 20 women per group, we will be able to detect a mean difference of at least 0.37 standard deviation units in follicular levels of C-reactive protein and of insulin. In our previous study, we found follicular fluid CRP differences of 3.2 μg/ml (2.7 vs. 5.9 μg/ml, respectively) between normal weight and obese women [12]. Thus, we are confident that this sample size will be sufficient to detect clinically meaningful differences. Based on our experience, we expect that we will be unsuccessful in obtaining a good quality oocyte from approximately 33% of women enrolled. Therefore, we will enroll 30 women in each of the 4 groups (PCOS- standard of care, PCOS-intervention, no PCOS- standard of care, no PCOS-intervention) to assure that we will have at least 20 oocytes per group.

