### Contingencies

Recruitment may be challenging because we will be enrolling women who want to conceive as soon as possible and who may choose to immediately attempt in vitro fertilization rather than wait. However, these women will have a high motivation to achieve the best outcomes for their treatments, which are known to be improved by increasing physical activity and adhering to a healthy diet.

Sedentary women with obesity may also be reluctant to participate in PA or implement dietary changes. To counter compliance issues, participants will have twice-weekly phone contact with the trained professionals at ACNC. We believe participants randomized to the intervention group will have a higher rate of participation due to their urgency to conceive and lack of pregnancy symptoms that can make it more difficult to engage in exercise routines. While we will track diet compliance through daily food diaries, this approach cannot fully capture non-compliance with the dietary intervention. For this reason, we will collect red blood cells for analysis of enrichment in PUFAs in the intervention groups. Stool will also be collected to enable a secondary measure of microbiome differences across groups. We anticipate that intervention participants, whose diet will contain significantly more fiber, fruits, and vegetables compared to the typical American diet, should be readily distinguishable from the control group.

The research team at the ACNC has experience in all aspects of the proposed study. Therefore, minimal problems are expected regarding the techniques proposed. One potential concern is participant non-compliance or drop out. Accordingly, we anticipated this issue in our sample size calculation. Absence of an effect of the intervention is also a concern; in this case, a study with a longer intervention or an additional exercise intervention would be explored for future studies.

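### The sample size shows no room for the drop-out that Contingencies says it covers, and 30 women per group does not assure 20 oocytes

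*Protocol article*

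**What the plan says.** Three parts of the protocol article bear on this point.

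- **Timing of retrieval.** Under Interventions, the programme "will take place during the weeks leading up to oocyte retrieval and continue until 2 weeks after implantation", with an expected length of 8–12 weeks. Under Standard of care, the other arm is released from any such delay: "Participants will not be required to wait 8 weeks prior to their retrieval procedures since no intervention is needed".
- **Drop-out.** The Contingencies section says: "One potential concern is participant non-compliance or drop out. Accordingly, we anticipated this issue in our sample size calculation". It gives no rate.
- **The calculation.** The Sample size section works from 20 women per group. It then makes one allowance: "we expect that we will be unsuccessful in obtaining a good quality oocyte from approximately 33% of women enrolled". From this it sets enrolment at 30 in each of the four groups (PCOS status by treatment), "to assure that we will have at least 20 oocytes per group".

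The section on oocyte, cumulus cell and follicular fluid collection adds that a retrieval may leave no eggs beyond those needed for treatment. It then says: "In this case, only follicular fluid will be obtained".

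**The concern.** Contingencies tells the reader that drop-out is already in the sample size. The calculation it points to names a single cause of loss, failure to obtain a usable oocyte, and that cause alone takes 30 down to 20. On a plain reading the two sections do not agree.

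The stated purpose of enrolling 30 is also too strong. Dividing the target by the expected success rate makes the average yield equal to the target. It does not make the target a floor.

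Oocyte gene expression is a primary outcome. It can be measured only in women who reach retrieval and have a spare, usable oocyte. If the team and its funder believe that 20 per group is secured with drop-out included, they may be surprised by a shortfall that the protocol's own figures already predict.

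**Working it through.** **Inputs from the Sample size section:** target 20 per group; failure rate 33% of women enrolled, so success 0.67; enrolment 30 per group; four groups. The section moves from 20 women to 20 oocytes, so one oocyte per woman is counted here.

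**Step 1: reproduce the plan's figure.** 20 / (1 − 0.33) = 29.85, rounded up to 30. The plan's 30 is therefore the 33% allowance and nothing else.

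**Step 2: what is left for drop-out.** 30 × 0.67 = 20.1, a margin of 0.1 oocyte per group. With one woman lost, 29 × 0.67 = 19.4, already below 20.

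**Step 3: is 20 assured with no further loss?** Let X be the number of women with a usable oocyte, X ~ Binomial(30, 0.67), with women independent.

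- One group: P(X ≥ 20) = 0.600.
- All four groups, taken as independent: 0.600⁴ = 0.130.

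This step needs no assumed drop-out rate. It also covers the reading in which the 33% already includes drop-out, because the success rate is then still 0.67.

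**Step 4: if drop-out comes on top of the 33%.** The article gives no rate, so d is assumed and shown as a range. Expected yield is 30 × (1 − d) × 0.67, and the chance of 20 is P(X ≥ 20) with X ~ Binomial(30, 0.67(1 − d)).

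| Assumed d | Expected oocytes per group | Chance that a group reaches 20 |
|---|---|---|
| 0% | 20.1 | 0.60 |
| 5% | 19.1 | 0.45 |
| 10% | 18.1 | 0.30 |
| 20% | 16.1 | 0.10 |
| 30% | 14.1 | 0.02 |

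**Step 5: cost in precision.** If both compared groups lose a fraction d, the standard error of a difference in means grows by 1/√(1 − d). That is 1/√0.9 = 1.05 at 10% and 1/√0.8 = 1.12 at 20%, so 5% and 12% wider. This is a guide to scale only, since the oocyte data are to be analysed with DESeq2.

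**Step 6: follicular fluid.** It is still collected when no oocyte is spare, so the 33% does not apply to it in the same way. A group of 30 can lose 10 women and keep 20, before blood-contaminated samples are set aside.

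**The case against.** **The 33% may already include drop-out.** It is a percentage of women enrolled, not of women retrieved, and it rests on the team's experience. A woman who leaves is an enrolled woman without an oocyte, so the two sections could be reconciled. This stands as a possible reading, although the only cause named is failure to obtain a good-quality oocyte. It does not rescue the assurance of 20, because step 3 holds on either reading.

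**The complaint turns on one word, and the loss of precision is small.** Inflating by the expected loss is ordinary practice, and a shortfall of two oocytes per group costs about 5% in standard error. The section's power statement also concerns follicular C-reactive protein and insulin, which are largely unaffected. All of this stands and keeps the point modest.

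**A stronger reading that a reader might infer.** Because only the intervention arm is expected to delay retrieval, one might conclude that drop-out will concentrate there and leave a selected group. The article does not support that as a finding:

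- Its remark about "women who want to conceive as soon as possible and who may choose to immediately attempt in vitro fertilization rather than wait" explains why recruitment may be hard. It concerns women who decline to enrol.
- The sentence "We believe participants randomized to the intervention group will have a higher rate of participation due to their urgency to conceive" goes on to mention the absence of pregnancy symptoms and follows a remark on compliance. It is about engaging with the programme, not about tolerating a wait.
- Data collection methods expects 8–12 weeks on average between visits 1 and 3 without separating the arms, so the real difference in waiting may be small.
- The intervention arm receives free meals, coaching, gym reimbursement, weekly payments and a bonus, all of which may help retention.
- Nothing in the article excludes intervention women who go to retrieval early.

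Unequal drop-out remains a possible risk. The article gives no rate for either arm, and the size of any selection effect cannot be derived from it.

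**Conclusion.** The point holds in a limited form. On the plain reading, the statement that drop-out was anticipated is not borne out by the calculation: the step from 20 to 30 is fully used by the 33% oocyte failure. On either reading, 30 per group does not assure 20 oocytes. The chance is about 60% in one group and about 13% in all four, assuming independent women, independent groups and a true success rate of 0.67.

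If drop-out is additional, the expected yield falls to about 18 per group at an assumed 10% and about 16 at 20%. The effect on precision is modest and confined mainly to the oocyte gene-expression outcome. The waiver for the standard of care arm is reasoned and is not at fault.

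**What to change.** Keep 30 women per group and change the text.

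1. In the Sample size section, replace the assurance of at least 20 oocytes with an expected yield: about 20 per group before drop-out, and fewer with it, for example about 18 at an assumed 10% and 16 at 20%.
2. In the same place, state whether the 33% includes drop-out.
3. If it does not, remove or correct the statement in Contingencies that drop-out was anticipated in the calculation.

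These are wording changes and cost nothing in recruitment, procedures or budget.

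Larger enrolment is not recommended. Restoring an expected 20 in the two intervention groups takes 20 / (0.67 × (1 − d)) women per group, which is 34, 38 or 43 for d = 10%, 20% or 30%. Under the same binomial model, the chance that such a group reaches 20 is still only 0.64, 0.61 or 0.58. That means 8, 16 or 26 more women across the two groups, each with 8–12 weeks of meals, for about the same chance as 30 women give with no drop-out, in a trial that already expects recruitment to be difficult.
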